**Comment to Serious Assessment for Invasive and Malignant Cancers:**

Adverse Events (AEs) for malignant tumours reported during a study should generally be assessed as Serious AEs. If no other serious criteria apply, the ‘Important Medical Event’ criterion should be used. In certain situations, however, medical judgement on an individual event basis should be applied to clarify that the malignant tumour event should be assessed and reported as a Non-Serious AE.

However, the instruction above applies only when the malignant tumour event in question is a new malignant tumour (i.e., it is not the tumour for which entry into the study is a criterion and that is being treated by the IP under study and is not the development of new or progression of existing metastasis to the tumour under study). Malignant tumours that – as part of normal, if rare, progression – undergo transformation (e.g., Richter’s transformation of B cell chronic lymphocytic leukemia into diffuse large B cell lymphoma) should not be considered a new malignant tumour.

## Recording of adverse events

### Time period for collection of adverse events

Adverse Events, including Serious Adverse Events, will be collected from time of signature of informed consent, throughout the treatment period and up to and including the 30-day follow-up period. All ongoing and any new AEs/SAEs identified during the 30 calendar days follow up period after last dose of study medication must be followed to resolution.

#### Adverse events after the 30 day follow up period

For Pharmacovigilance purposes and characterisation, any case of MDS/AML or new primary malignancy occurring after the 30 day follow up period should be reported to AstraZeneca Patient Safety whether it is considered a non-serious AE (e.g. non-melanoma skin cancer) or SAE, and regardless of investigator’s assessment of causality or knowledge of the treatment arm.  Investigators will be asked during the regular follow up for overall survival if the patient has developed MDS/AML or a new primary malignancy and prompted to report any such cases.

At any time after a patient has completed the study, if an Investigator learns of any SAE including sudden death of unknown cause, and he/she considers there is a reasonable possibility that the event is causally related to the investigational product, the investigator should notify AstraZeneca, Patient Safety.

Otherwise, after study treatment completion (i.e. after any scheduled post treatment follow-up period has ended) there is no obligation to actively report information on new AEs or SAEs occurring in former study patients. This includes new AEs/SAEs in patients still being followed up for survival but who have completed the post treatment follow up period (30 days).

### Follow-up of unresolved adverse events

Any SAE or non-serious adverse event that is ongoing at the time of the 30-day follow up, must be followed up to resolution unless the event is considered by the investigator to be unlikely to resolve, or the patient is lost to follow up. AstraZeneca retains the right to request additional information for any patient with ongoing AE(s)/SAE(s) at the end of the study, if judged necessary.

### Variables

The following variables will be collect for each AE:

- AE (verbatim)
- The date when the AE started and stopped
- Maximum CTCAE grade
- Whether the AE is serious or not
- Investigator causality rating against the IP (yes or no)
- Action taken with regard to IP
- Outcome

In addition, the following variables will be collected for SAEs:

- Date AE met criteria for serious AE
- Date Investigator became aware of serious AE
- AE is serious due to (provide all seriousness criteria applicable)
- Date of hospitalisation (if applicable)
- Date of discharge (if applicable)
- Probable cause of death (if applicable)
- Date of death (if applicable)
- Autopsy performed (yes or no; if yes provide report) (if applicable)
- Causality assessment in relation to study procedure(s)
- Causality assessment in relation to Other medication
- Description of AE

Severity of AE

For each episode of an adverse event, all changes to the CTCAE grade attained as well as the highest attained CTC grade should be reported.

It is important to distinguish between serious and severe AEs. Severity is a measure of intensity whereas seriousness is defined by the criteria in Section 6.2. An AE of severe intensity need not necessarily be considered serious. For example, nausea that persists for several hours may be considered severe nausea, but not a SAE unless it meets the criteria shown in Section 6.2. On the other hand, a stroke that results in only a limited degree of disability may be considered a mild stroke but would be a SAE when it satisfies the criteria shown in Section 6.2.

The grading scales found in the National Cancer Institute (NCI) CTCAE version 4.0 will be utilised for all events with an assigned CTCAE grading. For those events without assigned CTCAE grades the recommendation is that the CTCAE criteria that convert mild, moderate and severe events into CTCAE grades should be used.

A copy of the CTCAE version can be downloaded from the Cancer Therapy Evaluation program website (http://ctep.cancer.gov).

### Causality collection

The investigator will assess causal relationship between Investigational Product and each Adverse Event, and answer ‘yes’ or ‘no’ to the question ‘Do you consider that there is a reasonable possibility that the event may have been caused by the investigational product?’

For SAEs causal relationship will also be assessed for other medication and study procedures. Note that for SAEs that could be associated with any study procedure the causal relationship is implied as ‘yes’.

A guide to the interpretation of the causality question is found in Appendix A ‘Additional Safety Information’ to the Clinical Study Protocol.

### Adverse events based on signs and symptoms

All AEs spontaneously reported by the patient or care provider or reported in response to the open question from the study personnel: *‘Have you had any health problems since the previous visit/you were last asked?’*, or revealed by observation will be collected and recorded in the CRF. When collecting AEs, the recording of diagnoses is preferred (when possible) to recording a list of signs and symptoms. However, if a diagnosis is known and there are other signs or symptoms that are not generally part of the diagnosis, the diagnosis and each sign or symptom will be recorded separately.

### Adverse events based on examinations and tests

The results from protocol mandated laboratory tests and vital signs will be summarised in the clinical study report. Deterioration as compared to baseline in protocol-mandated laboratory values, vital signs and ECG abnormalities should therefore only be reported as AEs if one of the following is met:

- Any criterion for an SAE is fulfilled
- Causes study treatment discontinuation
- Causes study treatment interruption
- Causes study treatment dose reduction
- The investigator believes that the abnormality should be reported as an AE

If deterioration in a laboratory value/vital sign is associated with clinical signs and symptoms, the sign or symptom will be reported as an AE and the associated laboratory result/vital sign will be considered as additional information. Wherever possible the reporting Investigator uses the clinical, rather than the laboratory term (e.g., anaemia versus low haemoglobin value). In the absence of clinical signs or symptoms, clinically relevant deteriorations in non-mandated parameters should be reported as AE(s).

Deterioration of a laboratory value, which is unequivocally due to disease progression, should not be reported as an AE/SAE.

Any new or aggravated clinically relevant abnormal medical finding at a physical examination as compared with the baseline assessment will be reported as an AE.

### Hy’s Law

Cases where a patient shows elevations in liver biochemistry may require further evaluation and occurrences of AST or ALT ≥ 3xULN together with total bilirubin ≥ 2xULN may need to be reported as SAEs. Please refer to Appendix B for further instruction on cases of increases in liver biochemistry and evaluation of Hy’s Law.

### Disease progression

Disease progression can be considered as a worsening of a patient’s condition attributable to the disease for which the investigational product is being studied. It may be an increase in the severity of the disease under study (DUS) and/or increases in the signs and symptoms of the cancer. The development of new, or progression of existing metastasis to the primary cancer under study should be considered as disease progression and not an AE (if the progression was ‘as expected’). Events, which are unequivocally due to disease progression, should not be reported as an AE during the study.

### New cancers

The development of a new primary cancer (including skin cancer) should be regarded as an AE and will generally meet at least one of the serious criteria (see Section 6.2). New primary cancers are those that are not the primary reason for the administration of the study treatment and have developed after the inclusion of the patient into the study. They do not include metastases of the original cancer. Symptoms of metastasis or the metastasis itself (if ‘as expected’) should not be reported as an AE/SAE, as they are considered to be disease progression.

### Lack of efficacy

When there is deterioration in the ovarian cancer, for which the study treatment(s) is being used, there may be uncertainty as to whether this is lack of efficacy or an AE. In such cases, unless the Sponsor or the reporting physician considers that the study treatment contributed to the deterioration of the condition, or local regulations state to the contrary, the deterioration should be considered to be a lack of efficacy and not an AE.

### Deaths

All deaths that occur during the study, or within the protocol defined 30 day post study follow up period after the administration of the last dose of study treatment, must be reported as follows:

- Death clearly the result of disease progression should be reported to the study monitor at the next monitoring visit and should be documented in the eCRF but should not be reported as an SAE.
- Where death is not due (or not clearly due) to progression of the disease under study, the AE causing the death must be reported to the study monitor as a SAE within 24 hours (see Section 6.2 for further details). The report should contain a comment regarding the co-involvement of progression of disease, if appropriate, and should assign main and contributory causes of death. This information can be captured in the ‘Death eCRF’.
- Deaths with an unknown cause should always be reported as a SAE. A post mortem maybe helpful in the assessment of the cause of death, and if performed a copy of the post-mortem results should be forwarded to AstraZeneca within the usual timeframes.

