## Study Design

This is a prospective, open-label, single arm, multi-centre interventional study to assess the clinical efficacy and safety of olaparib maintenance monotherapy as the tablet formulation in PSR high grade (serous or endometrioid) epithelial ovarian cancer patients (including patients with primary peritoneal and / or fallopian tube cancer).

Figure 1 Study Flow Chart

Notes: OC ovarian cancer; PR partial response; CR complete response; PFS progression free survival; PFS2 time to second progression; TFST time to first subsequent treatment; TSST time to second subsequent treatment; OS overall survival; TDT time to discontinuation of treatment;

Patients will be assigned to olaparib tablets p.o. 300 mg twice daily. They should initiate olaparib treatment within 8 weeks after their last dose of chemotherapy (last dose is the day of the last infusion).

Patients must have clinical and objective radiological tumour assessments according to RECIST 1.1 criteria at baseline and every 12 weeks relative to date of enrolment, until objective radiological disease progression as determined by the investigator. Patients could continue to receive olaparib for as long as determined by the investigator, until objective radiological disease progression or as long as in the investigator’s opinion they are benefiting from treatment in relation to other clinical assessments and they do not meet any other discontinuation criteria.

Once a patient has discontinued olaparib she will be managed as per local clinical practice but will remain in the study and data will be collected on subsequent treatments, progression and survival.

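### Protocol 6.3.11 and 6.3.1.1 give sites opposite instructions on whether a non-progression or unexplained death in survival follow-up must be reported as an SAE

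*Protocol*

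**What the plan says.** **The wide rule.** Section 6.3.11 of the protocol (Deaths) sets its scope as "All deaths that occur during the study, or within the protocol defined 30 day post study follow up period" counted from the last dose. Inside that scope, "Where death is not due (or not clearly due) to progression of the disease under study, the AE causing the death must be reported". Such an event counts as an SAE, goes to the study monitor, and has a 24-hour limit. The section adds: "Deaths with an unknown cause should always be reported as a SAE". Neither instruction depends on suspected causality. Only deaths clearly due to progression are exempt from SAE reporting.

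**Who is in the study.** Under section 1.5 a patient who stops olaparib "will remain in the study and data will be collected on subsequent treatments, progression and survival". Section 3.9.1 says that stopping the drug is not withdrawal unless consent is withdrawn. Section 9.3 ends the study only at the final patient's last visit.

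**The narrow rule.** Section 6.3.1 collects AEs and SAEs from consent to the end of the 30-day follow-up. Section 6.3.1.1 says that after this "there is no obligation to actively report information on new AEs or SAEs occurring in former study patients", and continues: "This includes new AEs/SAEs in patients still being followed up for survival" beyond the 30 days. Before that sentence it makes two exceptions:
- MDS/AML and new primary malignancy are reportable whenever they occur.
- After a patient has completed the study, the investigator should notify "any SAE including sudden death of unknown cause, and he/she considers there is a reasonable possibility that the event is causally related" to olaparib.

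**The schedule.** Table 3, for follow-up after treatment has stopped, ticks the Adverse Events row in both columns, including the one for second progression and survival. The row carries no footnote.

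**The concern.** A woman who dies a year after her last tablet, of a non-cancer or unknown cause, falls under both rules. One makes her death a 24-hour SAE report. The other says nobody need report it. Sites that each follow the protocol can therefore act differently, across the planned 20 to 35 centres in two countries.

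AEs and SAEs are the stated outcome measure for the safety objective (section 2.3), and the study has one arm. If reporting of late deaths varies by site, there is no comparator in which the same variation would also appear. Late unexplained deaths are also the cases in which an undiagnosed drug effect could go unnoticed, because the MDS/AML and new-malignancy exception needs a diagnosis.

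**Working it through.** This is mainly a matter of setting the text side by side. The plan states no figure to reproduce.

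**Step 1. Does 6.3.11 reach survival follow-up?** On its words, yes. Sections 1.5, 3.9.1 and 9.3 keep an off-treatment patient in the study until it ends. Section 6.2 defines an SAE as arising in any study phase and lists follow-up among them. Section 6.4 applies the 24-hour duty throughout the course of the study.

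**Step 2. Does 6.3.1.1 reach the same patient?** Yes. It names patients still followed for survival.

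**Step 3. Compare the instructions for a death more than 30 days after the last dose, in a patient still in survival follow-up.**

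| Death | Section 6.3.11 | Section 6.3.1.1 | Agree? |
| --- | --- | --- | --- |
| Clearly due to progression | Not an SAE; eCRF and next monitoring visit | No SAE duty | Yes |
| MDS/AML or new primary malignancy | SAE | Report to Patient Safety | Yes on the need to report |
| Other or unknown cause, judged possibly related | SAE | Notify, but worded for patients who have completed the study | Only if the exception extends to survival follow-up |
| Other non-progression cause, not judged related | SAE within 24 hours | No obligation | **No** |
| Unknown cause, not judged related | Always an SAE | No obligation | **No** |

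The last two rows are the contradiction. The third row is an ambiguity.

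**Step 4. Scale.** Inputs: about 220 patients (section 8.2) and a final analysis at about 60% OS maturity (sections 4.4.5 and 8.5).

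Expected deaths = 0.60 × 220 = 132.

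The number in the conflicting rows is at most f × 132, where f is the share of all deaths that are both late and not clearly due to progression. The documents do not give f. As an assumption only:
- f = 5%: 0.05 × 132 = 6.6, about 7 deaths
- f = 20%: 0.20 × 132 = 26.4, about 26 deaths

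Deaths that meet a 6.3.1.1 exception must be subtracted. The range only illustrates scale, and the contradiction does not depend on it.

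**The case against.** The best counter-argument is that the protocol, read as a whole, already favours the 30-day window. The second limb of 6.3.11 describes 30 days after the last dose as a post-study period, which makes sense only if *study* there means study treatment. Under the wide reading that limb is almost redundant. Section 6.3.1.1 is the specific provision for late events, 6.3.1 sets the same window, and 3.9.1 requires new SAEs to be reported for 30 days and then refers the reader to 6.3.1.1. Because 6.3.1.1 counts survival follow-up among former study patients, its causality exception may reach them as well. The ticked row in Table 3 could be meant for following up ongoing events and for the MDS/AML prompts.

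Most of this stands as a reading of intent: the narrow window is probably what was meant. It does not remove the conflict. The narrow reading of 6.3.11 goes against the protocol's own statements on who remains in the study, while 6.2, 6.4 and Table 3 point the other way. On unknown-cause deaths, even a generous reading leaves *always* in one section and *only if suspected* in the other.

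It is also fair to say that the unseen SAP may limit tabulated SAEs to an on-treatment window. That would reduce the effect on the tables but would not tell sites what to report.

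**Conclusion.** The point holds as an internal contradiction in a 24-hour reporting duty. It is confined to deaths in survival follow-up that are of non-progression or unknown cause and fall outside the 6.3.1.1 exceptions. The consequence is that the collected fatal-SAE count can differ by site. The finding rests on the text alone, and its size cannot be derived from the documents.

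A reader might infer three stronger conclusions that the documents do not support:
- **The fatal-SAE count would change several-fold or become uninterpretable.** That needs both the share of late non-progression deaths and the number of fatal SAEs within 30 days. Neither is given.
- **Late MDS/AML deaths would be lost.** Section 6.3.1.1 keeps these reportable whatever the causality, and investigators are asked about them at survival follow-up. Only a case never diagnosed could be missed.
- **The efficacy results are at risk.** They are not. Deaths are collected for survival under either reading, so PFS and OS are unaffected.

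**What to change.** Reconcile 6.3.11, 6.3.1, 6.3.1.1 and the Adverse Events row of Table 3 to one stated reporting window. The sponsor may choose which, but cannot keep both. One way that uses only rules already in the protocol:

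1. In 6.3.11, replace *during the study* with the window in 6.3.1 (consent to 30 days after the last dose), and refer to the 6.3.1.1 exceptions for later deaths.
2. In 6.3.1.1, state that those exceptions, including the one for SAEs judged possibly related, also apply to patients still in survival follow-up.
3. Footnote the Adverse Events row in Table 3 to say what is collected after the 30 days.
4. Record date and cause of every later death on the existing Death eCRF, so that fatal SAEs within 30 days can be shown separately from later deaths.

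This needs no new category of late SAE. Making all late unexplained deaths reportable would be a change of policy, not a reconciliation.

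The cost is minor wording in an amendment and re-notification of sites. The Death eCRF and the 12-weekly survival contacts already exist. Reports already made under either reading cannot be harmonised by wording alone, which is a further reason to have cause and date of death on the eCRF for all patients.

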## Reporting of serious adverse events

All SAEs have to be reported, whether or not considered causally related to the investigational product, or to the study procedure(s). All SAEs will be recorded in the CRF.

If any SAE occurs in the course of the study, then investigators or other site personnel inform the appropriate AstraZeneca representatives immediately, but **no later than 24 hours** of when he or she becomes aware of it.

The designated AstraZeneca representative works with the investigator to ensure that all the necessary information is provided to the AstraZeneca Patient Safety data entry site **within 1 calendar day** of initial receipt for fatal and life-threatening events and within 5 calendar days of initial receipt of all other SAEs.

For fatal or life-threatening adverse events where important or relevant information is missing, active follow-up is undertaken immediately. Investigators or other site personnel inform designated AstraZeneca representatives of any follow-up information on a previously reported SAE within one calendar day i.e., immediately but **no later than 24 hours** of when he or she becomes aware of it.

Once the investigators or other site personnel indicate an AE is serious in the EDC system, an email alert is sent to the designated AstraZeneca representative.

If the EDC system is not available, then the investigator or other study site personnel reports a SAE to the appropriate designated AstraZeneca representative by telephone.

The designated AstraZeneca representative will advise the investigator/study site personnel how to proceed.

The reference document for definition of expectedness/listedness is the IB.

## Overdose

There is currently no specific treatment in the event of overdose with olaparib and possible symptoms of overdose are not established.

Olaparib must only be used in accordance with the dosing recommendations in this protocol. Any dose or frequency of dosing that exceeds the dosing regimen specified in this protocol should be reported as an overdose.

Adverse reactions associated with overdose should be treated symptomatically and should be managed appropriately.

- An overdose with associated AEs is recorded as the AE diagnosis/symptoms on the relevant AE modules in the CRF and on the Overdose CRF module.
- An overdose without associated symptoms is only reported on the Overdose CRF module.

If an overdose on an AstraZeneca study drug occurs in the course of the study, then the investigator or other site personnel inform appropriate AstraZeneca representatives immediately, or **no later than 24 hours** of when he or she becomes aware of it.

The designated AstraZeneca representative works with the investigator to ensure that all relevant information is provided to the AstraZeneca Patient Safety data entry site.

For overdoses associated with a SAE, the standard reporting timelines apply, see Section 6.4. For other overdoses, reporting must occur within 30 days.

